### **3.10 Sample size**

Each series in our design includes at least 8 measurement time-points (intervals). In 2017, the Alberta Children's Hospital and Stollery Children's Hospital provided mental healthcare to 150–200 children/youth per month. Based on an anticipated consent rate of 75% and 1-month follow-up rate of 75% during each phase, we will have  $\geq 50$  patients/interval. We conducted preliminary calculations for the series with the fewest number of data points (8) and patients (50/month) using a 2-sample t-test comparing mean values in the pre-implementation phase to those in the maintenance phase. These calculations assume no serial autocorrelation and a sustained effect of the bundle, which is justified based on the PDSA cycles that will have occurred. With at least 800 patients in both the pre-implementation and maintenance phases, respectively, we will have 90% power to detect an absolute improvement as small as 1.9 units on the SCWBS/WEMWBS (primary outcome), assuming a common standard deviation of 10 using a 2-sided 5% level of significance. Thus, we are well powered to detect a difference of 3 units at each study site, the minimally clinically important difference defined for this outcome. We are below the effect observed in other studies using the WEMWBS. These preliminary calculations will be updated once baseline data become available.

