### **3.11 Data analysis**

#### ***Child/youth wellbeing and family functioning***

Data will be summarized and presented as mean scores per month per site. Visual inspection of the multiple baseline time series plots will be used to refine the analytical approach, i.e., to examine the type of secular trends, to check for the presence of seasonal effects and any outliers, and to examine heterogeneity in baseline levels and secular trends across the 2 study sites. Our anticipated primary analytical approach will use site-specific linear segmented regression to analyze trends over time. The model for each series will include terms for the baseline level and pre-intervention trend, change in intercept and change in trend from the pre-implementation phase to each of the implementation and the maintenance phases. Durbin-Watson tests will be used to test for serial autocorrelation, and the autocorrelation coefficient will be accounted for in the analysis where necessary. A change in intercept and/or slope from the pre-intervention to the maintenance phase in the intervention sites will provide strong evidence of an effect due to the intervention. If the observed level and trends are sufficiently similar across the two sites, we will conduct a pooled mixed-effects regression analyses across the two sites to generate a combined estimate of the intervention effect. We will account for key child/youth

features as covariates in the model (age, self-reported gender, ethnicity, and acuity of concern at the initial ED visit).

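### Section 3.10 claims adequate power for 3 units at each site from a t-test of phase means, but the segmented regression in 3.11 has per-site power below 80% at every accrual the protocol supports (about 43% at the planned minimum)

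*Protocol*

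**What the plan says.** Protocol section 3.10 (Sample size) bases its calculation on the smallest series it expects, with 8 time points and 50 patients per month, "using a 2-sample t-test comparing mean values in the pre-implementation phase to those in the maintenance phase". It assumes no serial autocorrelation and a sustained effect. "With at least 800 patients in both the pre-implementation and maintenance phases, respectively", it reports 90% power for a difference of 1.9 units, "assuming a common standard deviation of 10 using a 2-sided 5% level of significance". From this it concludes that "we are well powered to detect a difference of 3 units at each study site", and it identifies 3 units as the minimally clinically important difference. It calls the calculations preliminary and says they will be updated when baseline data are available.

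Section 3.11 (Child/youth wellbeing and family functioning) states: "Our anticipated primary analytical approach will use site-specific linear segmented regression to analyze trends over time". Besides a baseline level and a pre-intervention trend, the model has "change in intercept and change in trend from the pre-implementation phase to each of the implementation and the maintenance phases". Autocorrelation is to be accounted for where needed. The two sites are pooled in a mixed-effects model only if their levels and trends are similar enough.

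Section 2.4 sets the phases at 12, 5 and 12 months.

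**The concern.** A t-test of two phase means takes the underlying trend to be flat. The segmented regression estimates that trend and projects it forward, as section 3.1 intends when it says effects are to be judged relative to the secular trend. Estimating a slope from 12 monthly points and extrapolating it over a further 5 months costs much precision, even with no autocorrelation. The power in 3.10 therefore belongs to a test that 3.11 does not plan to use.

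What is at stake is the per-site claim. Three units is the protocol's own threshold for a meaningful effect, and the primary analysis is specified site by site. If per-site power is well below what is stated, a non-significant result at one site says much less about a 3-unit effect than 3.10 implies.

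**Working it through.** **Inputs.** From 3.10: SD 10, two-sided 5%, at least 50 patients per monthly interval, no autocorrelation, sustained effect, target 3 units, 75% consent and 75% one-month follow-up, 150-200 children per month. From 2.4: 12, 5 and 12 months. From 3.11: six regression terms (level, trend, and a level and slope change for each of two later phases). From 3.5: about 20% of visits ineligible. From 1.1: 2,406 and 2,397 visits per year at the two hospitals, about 200 per month each, which supports reading 150-200 as a per-site figure.

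**Step 1: the protocol's own figure.** For two means, the 90%-detectable difference is (1.960 + 1.282) × 10 × √(2/n).
- n = 800 per phase: 3.242 × 10 × √(2/800) = 1.62 units. Power for 1.9 units is 96.7%, not 90%.
- n = 600 per phase (12 × 50): 1.87 units, with 90.8% power for 1.9. This matches the stated 1.9, but the stated n of 800 does not.
- One site, n = 400 per phase (8 × 50): power for 3 units is 98.9%.

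The stated 90% is thus conservative for a t-test, and the per-site claim is true for a t-test.

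**Step 2: variance under the 3.11 model.** Number the months 1-12 (pre), 13-17 (implementation) and 18-29 (maintenance). A monthly mean has variance 100/50 = 2. Each 12-month segment has a sum of squares about its mean of 143. The level change at month 18 is the fitted maintenance line minus the extrapolated pre-implementation line:
- extrapolated line: 2 × [1/12 + (18 − 6.5)²/143] = 2.016
- maintenance line: 2 × [1/12 + (18 − 23.5)²/143] = 0.590
- sum 2.606, so SE = 1.614

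The difference in phase means has variance 2 × 2/12 = 0.333. The ratio is 2.606/0.333 = 7.8.

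**Step 3: power for a 3-unit level change.** This uses the noncentral t. Each site has 29 − 6 = 23 df. Two sites of equal size have 46 df and SE divided by √2.

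| Patients/month per site | Basis | SE per site | Power per site | Power pooled |
|---|---|---|---|---|
| 50 | minimum in 3.10 | 1.614 | 43% | 73% |
| 67.5 | 150 × 0.8 × 0.75 × 0.75 | 1.389 | 54% | 85% |
| 90 | 200 × 0.8 × 0.75 × 0.75 | 1.203 | 67% | 93% |
| 112.5 | 200 × 0.75 × 0.75, no ineligible visits | 1.076 | 76% | 97% |

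A simulation of 40,000 series at 50/month gave 42.4% per site.

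**Step 4: detectable difference and sensitivity.**
- At 50/month, the 90%-detectable level change is 5.5 units per site and 3.8 units pooled.
- With 8/5/8 months at 50/month (the 8-point series that 3.10 cites), SE is 2.32 on 15 df and per-site power is 23%.
- With assumed first-order autocorrelation of 0.1 to 0.4, the 43% falls from 38% to 27%.
- For 80% per-site power, about 124 patients/month per site would be needed.

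**The case against.** The strongest defence is that 3.10 is open about its simplification. It names the t-test, states its assumptions, calls the result preliminary and promises an update; 3.11 calls its model anticipated and allows refinement after inspecting the series. That is fair, but the update is tied to baseline data, which can revise the SD or accrual. Nothing says that the method will change to match the regression, and the per-site conclusion carries no qualification.

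The second defence is that 50/month is a floor. This stands as a limit on the size of the problem. A reader might infer that the trial has 43% power, or that a 3-unit effect would usually be missed at a site. Both hold only at the floor: at 67.5-90/month, per-site power exceeds one half. Visits are not unique patients and repeat participants are excluded, so accrual is a range rather than a point.

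Third, a reader might infer that the trial as a whole is underpowered for 3 units. The documents do not support that. Pooled power is 85-93% at the accrual implied by the protocol's own rates, if pooling goes ahead and there is no autocorrelation.

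Fourth, the model might be simplified. Without a separate implementation segment (12/12 months, no gap), per-site power is 69% at 50/month and 82% at 67.5/month. That is not the model 3.11 states.

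Finally, no passage says that a null result will be read as absence of effect, so that consequence should not be attributed to the plan.

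**Conclusion.** The point holds. The power statement in 3.10 and the primary analysis in 3.11 concern different tests, and the claim of adequate power for 3 units at each site is not supported under the stated three-phase model. Per-site power is about 43% at the planned minimum and at most 76% over the accrual range the protocol supports, so it stays below 80% throughout.

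These figures assume SD 10, 12/5/12 months, no autocorrelation, a sustained step, and a test of the level change at the start of maintenance. Shorter series or positive autocorrelation would lower them. The pooled figures also assume two sites of equal size with a common effect. The failure of 800 per phase to reproduce exactly 90% for 1.9 units is a separate, minor discrepancy in the conservative direction. It should not be read as an inflated claim.

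**What to change.** In 3.10:
- Replace the t-test calculation with the power of the 3.11 level-change contrast, in closed form or by simulation, for 12/5/12 months.
- Delete the statement of adequate power for 3 units at each site.
- State that, at 50 patients/month with no autocorrelation, there is 90% power for about 5.5 units per site or about 3.8 units pooled. Tabulate power for 3 units over the assumed accrual range, with a sensitivity case for autocorrelation.
- Limit any statement of adequate power for 3 units to the pooled analysis, with its conditions given: similar levels and trends across sites, the accrual assumed and the autocorrelation assumed.

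Two further changes are optional and not needed for the correction. Making the pooled estimate primary would gain precision but override the present rule that pools only similar sites. Adding the 24-72 hour wellbeing score as a covariate would reduce the SE: with an assumed correlation of 0.5 or 0.6, per-site power at 50/month becomes about 54% or 60%. That score is taken after the ED visit and may absorb part of the effect, so the model without it should also be shown.

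The cost is a recalculation and some rewording. No extra patients are needed. The downside is a less favourable stated detectable difference.

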### **3.11 Data analysis**

#### ***Child/youth wellbeing and family functioning***

Data will be summarized and presented as mean scores per month per site. Visual inspection of the multiple baseline time series plots will be used to refine the analytical approach, i.e., to examine the type of secular trends, to check for the presence of seasonal effects and any outliers, and to examine heterogeneity in baseline levels and secular trends across the 2 study sites. Our anticipated primary analytical approach will use site-specific linear segmented regression to analyze trends over time. The model for each series will include terms for the baseline level and pre-intervention trend, change in intercept and change in trend from the pre-implementation phase to each of the implementation and the maintenance phases. Durbin-Watson tests will be used to test for serial autocorrelation, and the autocorrelation coefficient will be accounted for in the analysis where necessary. A change in intercept and/or slope from the pre-intervention to the maintenance phase in the intervention sites will provide strong evidence of an effect due to the intervention. If the observed level and trends are sufficiently similar across the two sites, we will conduct a pooled mixed-effects regression analyses across the two sites to generate a combined estimate of the intervention effect. We will account for key child/youth

features as covariates in the model (age, self-reported gender, ethnicity, and acuity of concern at the initial ED visit).

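### Autocorrelation is corrected only after a Durbin-Watson pre-test that is weak at 29 monthly points; fit AR(1) errors always, and test any slope change against an annual cycle

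*Protocol*

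**What the plan says.** Protocol section 3.11 (Child/youth wellbeing and family functioning) analyses monthly mean scores by site-specific linear segmented regression. The listed terms are a baseline level and trend, plus a change in intercept and in trend for each of the implementation and maintenance phases. That is six parameters per site, with no seasonal term.

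- **Autocorrelation:** "Durbin-Watson tests will be used to test for serial autocorrelation, and the autocorrelation coefficient will be accounted for in the analysis where necessary". No threshold and no estimator are named.
- **Trend shape, season, outliers and site differences:** "Visual inspection of the multiple baseline time series plots will be used to refine the analytical approach".
- **Pooling:** a combined mixed-effects analysis follows "If the observed level and trends are sufficiently similar across the two sites". No criterion is given.

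The section counts a change in intercept, in slope, or in both, between baseline and maintenance as firm evidence of an effect. The Process Outcomes part of 3.11 uses the same method for process measures and ED length of stay. Section 3.10 sizes the study on the assumption of no serial autocorrelation.

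**The concern.** A correction that depends on a significant pre-test protects the error rate only if the pre-test usually finds the problem. In a short series it often does not. The analysis then falls back on ordinary least squares, whose standard errors are too small exactly when autocorrelation is present but missed. The primary test would then reject too often, at both sites and for every outcome that uses the method.

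Season raises a related difficulty. Baseline covers one annual cycle, and maintenance starts 17 months after baseline starts, so the same calendar month falls at a different point in each phase. A cycle left out of the model can be absorbed by the phase-specific slopes, and a slope change alone is enough for a positive conclusion.

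**Working it through.** **The plan's own figure.** Section 3.10 claims 90% power for 1.9 units, "assuming a common standard deviation of 10" and "using a 2-sided 5% level of significance", with 800 patients per phase. SE = 10 × √(2/800) = 0.50. Then 1.9/0.50 = 3.80 and 3.80 − 1.96 = 1.84, which gives 96.7% power. The stated 90% is not reproduced; the 90% detectable difference would be 0.50 × (1.96 + 1.28) = 1.62. That mismatch is a separate matter and does not affect this point. What matters here is that the calculation takes autocorrelation as zero.

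**Inputs.**
- Phase lengths of 12, 5 and 12 months (section 2.4) give 29 points. With 6 parameters, 23 residual degrees of freedom remain.
- SD 10 and 50 patients per month (section 3.10) give a monthly-mean SE of 10/√50 = 1.41.
- Assumed, because the protocol gives neither: lag-1 correlation ρ of 0 to 0.4, and an annual cycle of 1 unit amplitude (0.5 and 2 also tried).
- Also assumed: a one-sided 5% Durbin-Watson test, with its critical value simulated for this design (about 1.75).

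**Autocorrelation.** Series with AR(1) errors and no intervention effect were simulated. The table gives Durbin-Watson detection and the type I error of the nominal 5% level-change test. Ranges reflect simulation error.

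| ρ | Durbin-Watson detects | OLS, no correction | Pre-test, then REML | Pre-test, then Prais-Winsten | REML always, ρ ≥ 0 |
|---|---|---|---|---|---|
| 0 | 5% | 5% | 5% | 4.7% | 3.5–4.1% |
| 0.2 | 18–19% | 10–11% | 9% | 9.4% | 6% |
| 0.3 | 29–30% | 14–15% | 11–12% | 12.1% | 7–8% |
| 0.4 | 42–43% | 19% | 13% | 16.8% | 8% |

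The cause is the understated OLS standard error. The true SD of the level change divided by its reported SE is 1.00, 1.21, 1.35 and 1.55 at ρ = 0, 0.2, 0.3 and 0.4. With REML always fitted but ρ unrestricted, type I error is 6.8%, 7.7%, 8.0% and 8.9%. Holding ρ non-negative therefore helps most at the low end.

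With only 8 + 5 + 8 = 21 points (section 3.10 guarantees at least 8 per series), detection falls to 13%, 19% and 23% at ρ = 0.2, 0.3 and 0.4.

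**Season.** An annual sine wave of amplitude 1 was projected on the six-parameter, 29-point design, taking the worst phase of the cycle.

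| Term | Largest bias | SE now | SE with one sine/cosine pair |
|---|---|---|---|
| Level change (units) | 1.18 | 1.61 | 1.74 (1.74/1.61 = 1.08) |
| Slope change (units/month) | 0.31 | 0.167 | 0.256 (0.256/0.167 = 1.53) |

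With independent errors and amplitude 1, the nominal 5% slope test rejects about 21% of the time on average over phase, and about 40% at the worst phase. The level test rejects about 6% on average and 8.5% at worst. A formal harmonic test finds the 1-unit cycle in only 17% of baselines and 38% of full series. At 2 units it finds it in 54% and 91%. With the sine/cosine pair in the model, both tests return to about 5% at every amplitude tried.

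**The case against.** **Detail for the analysis plan.** The estimator, the degrees-of-freedom correction and a numeric pooling rule commonly sit in a statistical analysis plan, and 3.11 describes its approach as anticipated. This stands for the pooling rule. It does not stand for the pre-test, which the protocol itself fixes as the route to any correction.

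**The error rates belong to an assumed procedure.** The protocol names neither a threshold nor an estimator, and Prais-Winsten is itself poor here: always used, it gives 11.6% at ρ = 0. That is fair, and it is why the REML column matters. With the better estimator the pre-test rule still gives 9% to 13%.

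**Autocorrelation may be small.** A reader might infer that the plan leaves standard errors too small in any event. The documents do not support that. At ρ = 0 they are correct. Earlier participants are excluded (sections 3.5 and 3.6), so monthly means come from different patients, and sampling variance of 1.41² = 2.0 dilutes any month-to-month process. A latent SD of 1 unit with latent correlation 0.6 gives an observed 0.6 × 1/(1 + 2) = 0.2. Reaching 0.4 takes a latent SD of 2: 0.6 × 4/(4 + 2) = 0.4. The harm is therefore conditional on ρ.

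**Season and the level change.** A reader might also infer that the level change could be a seasonal artefact. Its largest bias, 1.18, lies below its SE of 1.61 and the test barely moves. Nor do the 1.9- and 3-unit targets in 3.10 measure the seasonal harm: they belong to a comparison of phase means, and two full 12-month phases carry no annual bias. The exposure is in the slope.

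**Pooling.** The site-specific analysis is primary and pooling adds a combined estimate. An undefined similarity rule makes standard errors neither too small nor seasonally biased.

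**Conclusion.** The point holds in conditional form. If monthly means have a lag-1 correlation of 0.2 to 0.4, the Durbin-Watson rule misses it more often than not, and the nominal 5% level-change test runs at about 9% to 13% (REML correction) or 9% to 17% (Prais-Winsten). If there is no autocorrelation, the test is correct. The size rests on the assumed ρ, AR(1) errors, 29 points per site and a one-sided 5% pre-test. Error rates and detection rates for autocorrelation do not depend on the scale of the score.

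The seasonal point is secondary and concerns the slope. An assumed 1-unit cycle is smaller than the noise of a single plotted month, so inspecting the plot is a weak safeguard, yet it can shift the slope change by nearly twice its standard error (0.31/0.167 = 1.9). Larger cycles are easier to detect: a formal test on the full series usually finds one of 2 units.

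The pooling condition is only a point of clarity. The change is worth making because it is cheap and improves on the stated rule wherever ρ is positive.

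**What to change.** 1. **Autocorrelation (main change).** In section 3.11, replace the Durbin-Watson condition with a fixed rule: each site-specific segmented regression is fitted with AR(1) errors by REML, the coefficient held non-negative, with a small-sample degrees-of-freedom correction. Durbin-Watson results may be reported for description. Before the degrees-of-freedom correction (whose effect was not computed), type I error is about 3.5% to 4% at ρ = 0 and 6% to 8% at 0.2 to 0.4. The cost is wording and a slightly conservative test when there is no autocorrelation. The inflation is reduced, not removed: at ρ = 0.6 it is still 11.7%.

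2. **Season.** Provided the full 12-month phases are obtained, pre-specify at least a sensitivity analysis with one annual sine/cosine pair, and do not rest the conclusion on a slope change that disappears under it. In that analysis the level SE rises by 8% and the slope SE by 53%. With only 8 baseline and 8 maintenance months the level SE would go from 2.3 to 7.3, so the term is not practical there.

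3. **Pooling (clarity only).** Keep the site-specific analysis primary. State how similarity will be judged, or report the between-site difference in effect with its interval beside any pooled estimate.

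### The primary-outcome rule in 3.11 accepts a change in level and/or slope, with no required direction, no error control over the two terms, and no statement of whether one or both sites must show it

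*Protocol*

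**What the plan says.** Protocol section 3.11, under the heading on child/youth wellbeing and family functioning, makes the site the unit of primary analysis: "Our anticipated primary analytical approach will use site-specific linear segmented regression to analyze trends over time". Each site's model has a baseline level and trend, plus "change in intercept and change in trend from the pre-implementation phase to each of the implementation and the maintenance phases". That is six parameters per site, two of which (the maintenance level change and the maintenance slope change) bear on the main question.

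The rule for reading the result follows: "A change in intercept and/or slope from the pre-intervention to the maintenance phase in the intervention sites will provide strong evidence of an effect".

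A combined estimate is conditional: "If the observed level and trends are sufficiently similar across the two sites, we will conduct a pooled mixed-effects regression analyses across the two sites". No criterion for similarity is given.

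The only significance level in the protocol is in section 3.10: "assuming a common standard deviation of 10 using a 2-sided 5% level of significance". It belongs to a two-sample t-test of phase means, which has one contrast and no trend terms. The first objective in section 1.2 is that the bundle improves wellbeing.

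**The concern.** The protocol itself states the condition under which the primary result will be read as showing an effect, and leaves that condition open in three ways.

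- **Terms.** The and/or wording makes a change in either of two coefficients sufficient, which gives two chances per site with nothing to offset them.
- **Direction.** The objective is improvement, but the rule asks only for change. A fall in wellbeing would qualify, as would a higher level followed by a declining slope.
- **Sites.** The sentence refers to the sites in the plural without saying whether both must show the change or one is enough.

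At stake is the meaning of the primary conclusion. Its error rate cannot be stated until these choices are made. If they are made after the series have been inspected, they can follow the data, and section 3.11 already lets visual inspection of the plots refine the analysis.

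**Working it through.** **Inputs.** Phases of 12, 5 and 12 months (section 2.4), so 29 monthly points per site. Six parameters per site (section 3.11), leaving 29 − 6 = 23 residual degrees of freedom. Two sites (section 3.2). Two-sided 5% per term is an assumption carried over from section 3.10, because 3.11 gives no level. No autocorrelation, as section 3.10 assumes.

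**The plan's own figure.** Section 3.10 states "we will have 90% power to detect an absolute improvement as small as 1.9 units", with at least 800 patients per phase and SD 10.
- Standard error with 800 per phase: 10 × √(2/800) = 0.50. Power: Φ(1.9/0.50 − 1.96) = Φ(1.84) = 96.7%.
- Standard error with 600 per phase (12 months × 50): 10 × √(2/600) = 0.577. Power: Φ(3.29 − 1.96) = 90.8%.

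The stated 90% therefore fits about 600 per phase and is conservative at 800. This is not part of the present point. What matters here is that the calculation uses one contrast at two-sided 5%, which is not the rule in 3.11.

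**If the tests were independent.** Two terms at one site: 1 − 0.95² = 9.75%. Four terms over two sites: 1 − 0.95⁴ = 18.5%.

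**Under the protocol's model.** The two estimates at a site are correlated, so the rates were simulated with no true effect (200,000 series per case, ordinary least squares, t-tests on 23 degrees of freedom, 12+5+12 months). The protocol does not say where the intercept change is measured, and the result depends on it. If p is the per-site rate, the overall rate is 1 − (1 − p)² when either site suffices and p² when both are required.

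| Intercept change measured at | Correlation with slope change | Per site | Either site suffices | Both sites required |
|---|---|---|---|---|
| start of maintenance | 0.31 | 9.5% | 18.1% | 0.9% |
| time origin of the series | −0.85 | 7.3% | 14.1% | 0.5% |

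Other codings, the 8-point minimum series of section 3.10, and versions without a separate implementation segment gave 7.0-9.7% per site, 13.6-18.4% for either site and 0.5-0.9% for both.

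**Direction.** With the level change measured at the start of maintenance, about 4.7% of null series show a significant worsening in at least one term, which is about half of those that qualify. In about 24% of qualifying series the level and slope changes have opposite signs.

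**After the fix.** One joint two-degree-of-freedom F test of the maintenance level and slope changes gives 5.0% per site. Testing each term at 2.5% gives 4.8% per site. Over two sites, the joint test at 5% gives 0.05² = 0.25% if both are required and 1 − 0.95² = 9.75% if either suffices. At 2.5% per site, either-site error is 1 − 0.975² = 4.9%.

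**The case against.** The strongest reply has four parts.

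**A statistical analysis plan may settle this.** Levels, multiplicity and term coding are commonly left to such a plan, and 3.11 describes its approach as anticipated. That is fair for missing detail, and the choice of coding is such a detail. The and/or rule is not missing, however. The protocol states it, and a later plan would have to override it.

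**The 18% is one reading.** A reader might infer that a change at either site counts, and so that the trial's error rate is 18% against a stated 5%. The text does not say so. It speaks of the sites together and could equally require both, which gives under 1%. Nor is 5% stated for these regression terms. This part of the objection stands: 18% is the top of a range.

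**Lack of direction does not inflate error.** A two-sided 5% test already covers both tails, so accepting a worsening adds nothing to the rates above. This also stands. If only improvements counted, the rate would be 4.2-5.0% per site and 8.1-9.8% for either site. The matching nominal rate would then be 2.5% per term, so the near-doubling from two terms remains. The harm from the missing direction is one of interpretation: a harmful or mixed pattern meets the same wording as a benefit.

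**Autocorrelation.** A reader might add further inflation from serial correlation. The protocol gives no value for it and plans to test for it and account for it where needed, so nothing is added here.

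It would also go too far to insist on a pooled level change as the primary test. Sections 3.10 and 3.11 are built around inference at each site, and slope change is a legitimate target in an interrupted time series.

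**Conclusion.** The rule is badly fixed as written. At two-sided 5% per term and without autocorrelation, it gives about 7-10% false positives per site, and every coding tried exceeds 5%. The overall rate runs from under 1% to about 14-18%, depending only on a site requirement that the protocol does not state. It also lets a deterioration, or level and slope changes of opposite sign, count as showing an effect, although the objective is improvement. These sizes rest on three assumptions: the 5% level is borrowed from section 3.10, residuals are independent, and all 29 monthly points are available. The documents do not support a single figure such as 18% as the trial's error rate.

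**What to change.** In section 3.11, replace the and/or sentence with a rule that has these parts:

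1. One prespecified primary test per site at two-sided 5%. This is either a joint two-degree-of-freedom test of the maintenance level and slope changes, or one named contrast between the maintenance phase and the extrapolated pre-implementation trend.
2. A result counts as evidence of benefit only if the estimated maintenance-phase effect is higher wellbeing. The joint test has no direction of its own, so the quantity that supplies the sign must be named. One option is the average difference from the extrapolated trend over the maintenance months.
3. A statement of whether both sites must meet the rule. If either suffices, test each site at 2.5%.
4. The separate level and slope changes reported as supporting estimates with confidence intervals.

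These choices should be fixed before the outcome series are viewed. The change takes a few sentences and keeps the site-specific design. The sponsor can no longer claim an effect on whichever single term happens to be significant. Requiring both sites, or splitting the level between them, also costs some power, which can be assessed when the section 3.10 calculations are updated with baseline data, as already planned.
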